### Sample size calculation

At our institution, we have observed a symptomatic vasospasm rate of approximately 45%. The cure rate of SGB in the treatment of progressive CVS was reported as 39% in another trial [31]. Therefore, we hypothesize a positive effect size of 40% for e-SGB compared with the baseline rate. Finally, using PASS 15, a total of 228 patients were needed to detect the difference (27% in the treatment arm vs. 45% in the control arm) in the primary outcome with 80% power and a two-sided alpha of 0.05, allowing for a 5% loss to follow-up. An interim analysis will be performed when 50% of the required sample size is recruited.

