### Statistical analysis

All efficacy and safety analyses will be analyzed on both a per-protocol and intention-to-treat basis. The intent-to-treat (ITT) population will comprise all subjects randomized to receive e-SGB and with the completed assessment of symptomatic CVS. The per-protocol (PP) population will consist of all subjects in the ITT population not identified as protocol violators (i.e., no obvious Horner’s syndrome after e-SGB, etc.). These protocol violations will be shown in a listing. Subjects with puncture interruption and abandonment due to various reasons are considered to have failed e-SGB and will be excluded from any form of analysis. The decision to exclude a subject from the PP population will be made prior to breaking the blind. The primary outcome will be compared between groups using the Cochran–Mantel–Haenszel test. Postoperative cerebral hemodynamic changes measured at multiple planned time points will be compared using repeated-measures analysis of variance (ANOVA) with the Tukey–Kramer test. In addition, repeated-measures ANOVA will be utilized with a mixed-model approach (including time as a random effect), and the specific comparison of the change in each of those measurements between baseline and any specific time point will be tested using linear contrast. For other outcome data, categorical data will be analyzed by the *χ*^2^ test, and continuous data will be analyzed using Student’s *t* test or the Mann–Whitney *U* test. The rates of spasm, death, complications, and length of stay in the hospital and intensive care unit will be compared using Cox proportional hazards models. All analyses will be adjusted by age, sex, preoperative Hunt-Hess score, preoperative Fisher grade, and site of aneurysm. For the missing data, the last observation and the worst-case imputation scenarios will be used as the main interpolation method. A *p* value less than or equal to 0.05 (two-tailed alpha level) will be considered statistically significant.

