The goal of reducing CVS is to reduce DCI and improve aSAH patients’ neurological outcome. Although the 90-day mRS score will be observed, it will not be used as the primary outcome, which is one of the shortcomings of this trial. However, as a prospective trial with the main purpose of exploring the safety and effectiveness of e-SGB, choosing an appropriate intermediate indicator can avoid a large sample cost demand. It seems imprudent to recruit vast numbers of patients when the effect is not clearly understood. Vasospasm, especially with clinical symptoms, is strongly correlated with devastating outcomes. On the other hand, a more effective e-SGB treatment protocol (such as continuous block and site selection) is currently unclear and needs to be explored to facilitate further research on improving long-term prognosis. TCD will be conducted to monitor continuous cerebral hemodynamics in this trial, with the aim of observing the effect of e-SGB on postoperative cerebral hemodynamics and exploring the timeliness of e-SGB. A sudden and rapid increase in blood flow velocity at a certain point is often indicative of disease progression. Second, the effect of a single e-SGB may be limited by the several-hour half-life of ropivacaine in this trial. However, in the PTSD study, KristineL et al. performed SGB on patients only twice (with a two-week interval), assessed at week 8 postintervention, and showed significant differences between the two groups [37]. Additionally, Christopher et al. found that the proportion of progressive CVS patients whose blood flow velocity improved 24 h after a single SGB was greater than 50%, of which 34.1% remained normal [31]. These results indicate that although the half-life of local anesthetics is only a few hours, their effect is longer. Early and timely intervention may be more important for the prevention of CVS and DCI. In this trial, e-SGB will be completed within the first 72 h of aSAH in a clinical setting. Finally, the measurement of cerebral blood flow velocity by TCD can only reflect cerebral perfusion laterally, and there may be false positives. Therefore, CTP will be routinely completed in all patients before discharge with the aim of assessing the improvement in cerebral perfusion following e-SGB in this trial.

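### The mRS falls by default under simple tests that cannot carry the covariate adjustment the plan requires of all analyses, and the plan does not say which of those tests applies

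*Protocol article*

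**What the plan says.** All of the method statements are in one paragraph, Statistical analysis, in the protocol article. It assigns methods outcome by outcome:

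- Primary outcome: "The primary outcome will be compared between groups using the Cochran–Mantel–Haenszel test".
- Cerebral hemodynamics: repeated-measures ANOVA, also in a mixed-model form.
- Event rates and stays: "The rates of spasm, death, complications, and length of stay in the hospital and intensive care unit will be compared using Cox proportional hazards models".
- Everything else: "For other outcome data, categorical data will be analyzed by the" chi-square "test, and continuous data will be analyzed using" Student's t or the Mann–Whitney U test.

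A blanket rule follows: "All analyses will be adjusted by age, sex, preoperative Hunt-Hess score, preoperative Fisher grade, and site of aneurysm".

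The Secondary outcomes section lists the mRS score at discharge, 30 days and 90 days. The Statistical analysis section does not mention the mRS, so it belongs to the last group by default. Whether it counts there as categorical or continuous is not stated. On the purpose of the trial, the Discussion says: "The goal of reducing CVS is to reduce DCI and improve aSAH patients’ neurological outcome". It also counts not using the 90-day mRS as the primary outcome among the trial's shortcomings.

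**The concern.** There are two problems, one of consistency and one of efficiency.

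The chi-square, t and Mann–Whitney tests have no place for age, sex, Hunt-Hess score, Fisher grade and aneurysm site. No regression model is named for the outcomes sent to them. An analyst who runs the listed test breaks the adjustment rule, and one who adjusts must pick a model the plan does not name.

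The mRS is an ordered scale. A chi-square test on its levels ignores the order. Mann–Whitney uses the order but not the covariates. Student's t treats the levels as equally spaced and also leaves out the covariates. With the branch open, the choice could be made after the data are seen.

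The mRS is the trial's disability scale (the MMSE measures cognition). It is therefore the main evidence on whether less vasospasm means less disability. The sample size was set for a different endpoint, so an inefficient analysis makes it easier to miss a real functional benefit.

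**Working it through.** **Step 1: the plan's own figure.** Inputs from Sample size calculation: "27% in the treatment arm vs. 45% in the control arm", "with 80% power and a two-sided alpha of 0.05, allowing for a 5% loss to follow-up". With the unpooled variance formula,

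n per arm = (1.960 + 0.842)² × (0.45×0.55 + 0.27×0.73) / (0.45 − 0.27)² = 7.849 × 0.4446 / 0.0324 = 107.7, so 108.

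Total 216; 216 / 0.95 = 227.4, so 228. The stated size reproduces and is not at issue. The checks below use 108 evaluable patients per arm.

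**Step 2: assumptions.** The documents give no mRS distribution, no effect on the mRS and no covariate strength. Three control distributions over mRS 0–6 were assumed:

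- favourable: 20/27/18/12/10/4/9%
- middle: 12/20/18/15/15/8/12%
- flat: 1/7 in each level

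The treated distribution follows from a common odds ratio (OR) applied to every cumulative split.

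**Step 3: losing the order.** Simulated power at two-sided 0.05, 2000 trials per setting, no covariates:

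| Common OR | Chi-square, 7 categories | Chi-square, mRS 0–2 vs 3–6 | Mann–Whitney |
|---|---|---|---|
| 1.5 | 18–19% | 28–32% | 37–40% |
| 2.0 | 52–54% | 62–72% | 81–83% |
| 2.5 | 79–81% | 82–90% | 96% |

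Ranges run over the three distributions. At OR 1.0 the 7-category chi-square and Mann–Whitney rejected in 4.4% to 5.7% of trials, so their sizes are about right.

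An analytic check for the favourable distribution at OR 2:

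- Treated distribution: 33.3/30.6/14.8/8.2/6.0/2.2/4.7%.
- Chi-square: noncentrality = 108 × Σ(p − q)²/(p + q) = 7.98 on 6 degrees of freedom, which gives power 53%.
- Rank test: V = (216/12) × (1 − Σp̄³) = 18 × (1 − 0.049) = 17.1, where p̄ is the mean of the two arms' proportions. Then z = ln 2 × √17.1 = 2.87, and power = Φ(2.87 − 1.96) = 82%.

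Both agree with the simulation.

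**Step 4: losing only the covariates.** Favourable distribution, conditional OR 2.0, and one prognostic score with the stated standard deviation on the log-odds scale; 300 trials per setting, so the Monte Carlo standard error is about 2 to 3 points:

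| SD of prognostic score | Mann–Whitney | Adjusted proportional odds | Difference |
|---|---|---|---|
| 0 | 80% | 80% | 0 |
| 0.75 | 77% | 82% | 5 |
| 1.5 | 56% | 76% | 20 |

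A separate simulation (control distribution 15/25/20/12/10/6/12%, score worth 0.8 to 1.2 log-odds per SD, 400 trials per setting) gave Mann–Whitney 74% to 64% and adjusted proportional odds 83% to 79%, a difference of 9 to 15 points.

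**Step 5: which outcomes share the clash.** After removing the outcomes with a named method, the residual group holds the mRS, MMSE, delirium, abnormal CT perfusion and new cerebral infarction. All are sent to tests without covariates and all fall under the blanket adjustment rule.

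**The case against.** The strongest reply is that the plan never assigns the mRS to the chi-square test. The Secondary outcomes section words its binary outcomes as incidences but lists the mRS and MMSE as scores. That points to the second branch and, for a seven-level scale, to Mann–Whitney, a valid ordinal test already in the plan. This stands. A reader might infer that the plan discards the ordering and with it nearly 30 points of power. The text does not support that: the gap arises only if the mRS is treated as unordered categories, and without prognostic covariates Mann–Whitney and proportional odds have the same power (80% each).

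A reader might also infer that the mRS will be analysed unadjusted. The text does not settle that either, because it promises adjustment for everything. What it lacks is a named test that can deliver it.

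Could this be left to the statistical analysis plan or the supplement? The choice of a model could be. But here the article states both a list of tests and a rule they cannot obey, and a later document would have to override one of them. Supplement Part 3 is described as holding definitions.

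The remaining objections limit the size. The covariate gain rests on one idealised score rather than the five actual covariates. Eligibility (age 18 to 65, Hunt-Hess 1 to 3) narrows prognosis, so strong covariate effects are not assured. An OR of 2 on the mRS is also generous: the planned primary effect is itself an odds ratio of (0.45/0.55)/(0.27/0.73) = 2.2, and at OR 1.5 Mann–Whitney has only 37–40%. Finally, the clash is not peculiar to the mRS, so a remedy confined to it would leave the paragraph inconsistent. All of this is accepted.

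**Conclusion.** The point holds as an inconsistency within one paragraph. The mRS, and the other outcomes in the residual group, are sent to tests that cannot apply the required five-covariate adjustment, and the branch for the mRS is not fixed.

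The cost on the likelier reading, Mann–Whitney, is the covariate gain only: roughly 0 to 20 points of power at a conditional OR of 2, depending on assumed prognostic strength. On the less likely reading, seven unordered categories, the cost of losing the order is about 53% against 81% at a common OR of 2. Every power figure rests on assumed mRS distributions and effects; the contradiction itself rests on none.

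A reader should not infer any consequence for the main result. The mRS is one of several secondary outcomes, and neither the primary comparison nor the total of 228 depends on how it is analysed. The change is worth making because the mRS carries the trial's functional message.

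**What to change.** State that the mRS, with day 90 as the main time point and death scored 6, is compared by proportional-odds logistic regression on treatment and the five covariates already named. Report the common odds ratio with its 95% confidence interval, the proportion in each category by arm, and a check of proportionality.

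For the other outcomes now sent to simple tests, either name the matching adjusted regression (for example logistic for delirium, abnormal perfusion and new infarction; linear regression or ANCOVA for the MMSE) or state that they are compared without adjustment and limit the blanket sentence accordingly.

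The cost is wording only, because the outcomes and covariates are already part of the plan. The change should be fixed before unblinding. The one small downside is reliance on the proportional-odds assumption, which is approximate; the category proportions and the proportionality check let the reader judge it.

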### Discontinuation or withdrawal of study subjects

All subjects may voluntarily withdraw from the trial at any time for any reason, and the investigator may also discontinue the participation of any subject for a variety of reasons, primarily safety concerns or protocol violations.

### Data confidentiality management

All raw data will be collected through a paper case report form that is specially designed by researchers and placed in a dedicated locker. In addition, all researchers will follow the rules of professional confidentiality and must keep all personally identifiable and medical information of patients confidential. The paper clinical report form will be destroyed three years after the completion of the study. The electronic data will be encrypted and preserved after hiding the patient’s personal information, and access to the database will be restricted. All data confidentiality management shall be carried out by a designated data management team that is established by the principal investigator (PI) and independent statisticians. The PI will regularly inspect the content of the forms and the database to ensure accurate and timely data entry, follow-up, and recruitment progress as well as calculate withdrawal and loss-to-follow-up rates. At the end of this study, at least 20% of the clinical report forms will be randomly selected by the research department for integrity and authenticity review.

### Adverse event monitoring report and data monitoring committee

An adverse event (AE) is the development of an undesirable medical condition/complication or the deterioration of a preexisting medical condition following or during exposure to an intervention, whether considered causally related to the intervention. The expected harm/complications will be systematically collected by visiting each patient at each follow-up point, while the unexpected harm/complications will be collected through spontaneous reporting from the patients or physicians in charge. All study-related AEs will be recorded and closely monitored until they are resolved or stable or until it can be confirmed that the study treatment is not the cause of the events. The investigator will immediately report to the research department and advise the PI to determine the severity of the adverse event as soon as it occurs. In addition, it should be reported to the Ethics Committee (IRB) within 24 h, and the PI is responsible for reporting all AEs. The Data Monitoring Committee (DMC) will be responsible for monitoring clinical safety and reviewing all adverse events reported to the IRB to determine the risks and benefits of the study. The DMC is made up of specialists in anesthesiology, neuropathies, ethics, statistics, and methodology. If there were any severe adverse events (SAEs) associated with the study (grading criteria ≥ 3), the DMC was responsible for discussing whether to terminate the study (Table 2). In this study, all expected AE records will also be used as safety indicators to evaluate the safety of e-SGB, which is mainly completed by the DMC and reported in the final trial publications. If e-SGB significantly increases the risk of certain adverse events or is related to an unexpected SAE that deteriorates the patient’s condition, such as aneurysm rupture and rebleeding before clipping, we will emphasize this in the final results.

If the patient’s health is damaged due to participation in this study, we will be responsible for taking appropriate treatment measures. The sponsor, Beijing Tiantan Hospital, Capital Medical University, will bear the treatment expenses and pay corresponding economic compensation to the patients according to relevant national regulations.

### Ethics and dissemination

This study was approved by the Ethics Committee of Beijing Tiantan Hospital, Capital Medical University (Ethics No. KY 2021–023-02). In addition, it complies with the principles of the Helsinki Declaration, and the protocol (vol. 1.4; May 31, 2021) is written in accordance with the SPIRIT 2013 guidelines. The results of the study will be published in peer-reviewed journals, and the key findings will be presented at national or international conferences.

### Protocol amendment

Any decision to amend the trial protocol will be made by the PI. The PI will communicate with the research department before the implementation of the revised program if there are any modifications in the recruitment process of the study (such as changing the eligibility criteria, outcome indicators, statistical methods, etc.). Moreover, the PI shall obtain the approval of the Ethics Committee of Beijing Tiantan Hospital, Capital Medical University.

### Patients and public involvement

Patients and the public were not directly consulted during the formulation of the research questions or outcome measurements. None of the patients participated in the design, recruitment, or clinical implementation of this study. We will prepare a manuscript to present the trial results at the completion of the study. The final results of the study will also be disseminated to all study participants by their preferred method.

## Discussion

This is a prospective randomized controlled trial to explore the effectiveness and safety of e-SGB as a means of CVS prevention. DCI associated with CVS remains the main contributor to morbidity and mortality following aSAH. However, past efforts to address this issue have failed to make any considerable progress. Oral nimodipine has shown good curative effects but limited clinical application [5, 13]. Therefore, it is necessary to explore more feasible and effective treatments to reduce the incidence of CVS and DCI.

SGB is currently the most commonly used sympathetic block in medical practice. It has shown excellent curative effects on many intractable diseases, such as intractable angina, asthma, atopic dermatitis, hyperhidrosis, arrhythmias, hot flashes, and GI dysfunction. Recently, SGB was found to have a good therapeutic effect on posttraumatic stress disorder (PTSD) symptoms [37], which expanded its use to the field of neurology. Similarly, for vasospasm after aSAH, studies also found that SGB, as a remedial treatment, can alleviate progressive CVS and shows exciting potential [23, 29–33]. The expansion of applications of SGB to the whole body has been mirrored by expansion into pathophysiological conditions, which cannot be explained only by a direct lack of sympathetic innervation and consequent peripheral vasodilatation. As confirmed by numerous studies, it can modulate the immune response and diminish inflammation, which may be mediated by the generalized impact of sympathetic innervation on the immune system [21–29]. Therefore, similar to the “neuroprotection” of nimodipine, the potential protective effect of e-SGB after acute stress should not be ignored, as it may be the main mechanism for treating all of these diseases.

The goal of reducing CVS is to reduce DCI and improve aSAH patients’ neurological outcome. Although the 90-day mRS score will be observed, it will not be used as the primary outcome, which is one of the shortcomings of this trial. However, as a prospective trial with the main purpose of exploring the safety and effectiveness of e-SGB, choosing an appropriate intermediate indicator can avoid a large sample cost demand. It seems imprudent to recruit vast numbers of patients when the effect is not clearly understood. Vasospasm, especially with clinical symptoms, is strongly correlated with devastating outcomes. On the other hand, a more effective e-SGB treatment protocol (such as continuous block and site selection) is currently unclear and needs to be explored to facilitate further research on improving long-term prognosis. TCD will be conducted to monitor continuous cerebral hemodynamics in this trial, with the aim of observing the effect of e-SGB on postoperative cerebral hemodynamics and exploring the timeliness of e-SGB. A sudden and rapid increase in blood flow velocity at a certain point is often indicative of disease progression. Second, the effect of a single e-SGB may be limited by the several-hour half-life of ropivacaine in this trial. However, in the PTSD study, KristineL et al. performed SGB on patients only twice (with a two-week interval), assessed at week 8 postintervention, and showed significant differences between the two groups [37]. Additionally, Christopher et al. found that the proportion of progressive CVS patients whose blood flow velocity improved 24 h after a single SGB was greater than 50%, of which 34.1% remained normal [31]. These results indicate that although the half-life of local anesthetics is only a few hours, their effect is longer. Early and timely intervention may be more important for the prevention of CVS and DCI. In this trial, e-SGB will be completed within the first 72 h of aSAH in a clinical setting. Finally, the measurement of cerebral blood flow velocity by TCD can only reflect cerebral perfusion laterally, and there may be false positives. Therefore, CTP will be routinely completed in all patients before discharge with the aim of assessing the improvement in cerebral perfusion following e-SGB in this trial.

In conclusion, successful completion of this trial and validation of its primary hypothesis would have implications for CVS prevention. If the result is positive, it may provide a new direction for the prevention and treatment of CVS and DCI.

## Trial status

This clinical study is currently in the recruitment phase. The study recruited the first patient on July 1, 2021, and the estimated study completion date will be December 30, 2023.

## Data Availability

The datasets will be available from the primary investigator ([name], Email: [contact]) upon reasonable request after the publication of the study results.
